**Figure 1 F1:**
[figure not shown]
Flowchart of participants in the study.

### Blinding

2.3

The multidisciplinary care team, with a neurologist, a neuropsychologist, and a physiotherapist, will perform all evaluations without knowing if the patients were enrolled and the group to which the patients have been assigned, and they will not have a relationship with the physiotherapist who applies the intervention. An independent researcher, who will not know the identification of the groups, will carry out the statistical analysis.

### Inclusion criteria

2.4

Patients are included in the study if they meet the following inclusion criteria:

Patients of both sexes older than 50 years;Have a diagnosis of AD;Present mild or moderate cognitive impairment [Mini-mental State Examination (MMSE) score between 11 and 23 points included]^[68]^;Acceptance to participate in the study (enrollment in the study and signing of informed consent).

### Exclusion criteria

2.5

Patients are excluded if they present the following exclusion criteria:

Other associated pathologies that do not allow physical exercise due to having severe functional disability or being insecure (neurological diseases, severe cardiorespiratory pathology, etc);Impossibility to carry out the evaluation tests;Falls and other incidents or adverse events with severe consequences that cause disability and/or that do not allow the intervention to continue;Attendance at the MPEP is less than 75% in the total of the sessions between assessments. (Criterion applied to each period between assessments). Adherence control by the physiotherapist;Not performing the MPEP sessions for 2 or more consecutive weeks;Participate in another intervention program outside of this study, especially an exercise program (important intervention bias for the control group).

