Cognitive deficit in elderly patients with AD is associated with gait and balance disorders,^[21–25]^ and influences executive functions, attention, and visuospatial perception and enhances the risk of falls.^[25–29]^ Yoon et al^[21]^ suggest that impairment in balance and mobility begins during the subjective cognitive decline stage, especially among the most vulnerable populations of women and APOEε4 carriers; therefore, we can consider that the impairment in balance and mobility could represent a predictive surrogate marker of cognitive decline.^[21]^

Gait alterations appear in 50% of AD patients 3 years after the diagnosis of AD, and among these, 33% lose their capacity to walk. The prevalence of gait and balance alterations ranges from 9% to 52% depending upon the tool of assessment.^[20,22,30]^

There are many tests used to assess gait and balance in elderly, cognitive deficit, or AD patients, Tinetti Performance Oriented Mobility Assessment (POMA-T), timed up and go test (TUG), 1-leg balance test (OLB), and functional reach test (FR) being among the most used.^[16,20,21,30–34]^ For this reason, they were selected for use in our study.

Physical activity and exercise have been shown that can delay the progress of AD in an effective cost and sustainable manner.^[35]^ Currently, we know that exercise achieves improvement in cognition of elderly with AD,^[35,36]^ and have other beneficial effects improving physical function, increasing autonomy, and quality of life in patients with dementia.^[3,30,31]^ The studies showed evidence with different factors such as type of exercise, frequency, intensity, time, and follow-up of the intervention, participants, etc.^[30,35]^ Besides, pharmaceutical treatments fail to address the cause of AD, and only a few symptomatic treatments are currently available, providing modest improvements to patients’ livelihood, and normally with side effects that may include nausea, dizziness, and weight loss.^[2,37,38]^ Exercise has shown even more positive results in terms of mortality from different diseases and chronic conditions than poly-pills for cardiovascular prevention.^[39]^

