#### Primary outcome variables

2.7.1

The primary outcome measures are the change in gait, balance, and bone health status during the study follow-up.

Physical functions such as gait and balance will be assessed by the POMA-T and the TUG. Both of them are widely and easily used tools applied in clinical settings with older adults and AD patients.^[16,30]^ And bone health status will be assessed by quantitative ultrasound (QUS).^[79–81]^

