POMA-T: We will perform the original POMA-T 28-point version. It consists of a balance scale [Balance performance oriented mobility assessment (POMA-B)] and a gait scale [Gait performance oriented mobility assessment (POMA-G)]. POMA-B can score 16 points (sitting balance, get up and sit up from a chair, immediate standing balance in the first 3 to 5 seconds, standing balance, balance with eyes closed and turning balance 360°). POMA-G can score 12 points (initiation of gait, step height, step length, step symmetry, step continuity, path deviation, trunk stability, and walk stance). Less than 19 points means high risk of falls, between 19 and 24 means risk of falls, and between 24 and 28 means no disturbance in gait or balance. Therefore, the POMA-T's cutoff point that predicts moderate or high risk of falling and disturbance in balance and gait was 24.^[16,17,22,82,83]^TUG: Is an easy tool to evaluate the gait and balance. It measures the time in seconds for the subjects to get up from a standard armchair, walk 3 m, turn, walk back to the chair and sit down. The cut-off point for normal mobility is 12 seconds and values > 30 seconds indicate a high level of dependence,^[30,84,85]^ although other authors are somewhat stricter with the interpretation of the TUG, in such a way that with a time <10 seconds, it is considered normal; <20 seconds mobility difficulties and low or moderate risk of falls; > 20 mobility problems with need of help and high risk of falls.^[84]^Calcaneal QUS: The bone health status will be assessed by ultrasound bone densitometry/sonometry. It is a safe, radiation-free modality that provides precise quantitative assessment of skeletal status, useful information in elderly for identifying patients at risk of developing osteoporosis and for assessing their risk of future fracture.^[79,80,86]^ Bone mass we will measured at the calcaneus (95% of trabecular bone) by using QUS (Sahara Hologic Clinical Bone Sonometer; Hologic lnc., Waltham, MA). QUS parameters will be measured, but we consider the estimated BMD (g/cm^2^) and T-score (comparison of the average mineral density of the patient's bone with a healthy young people) as primary outcome, because some researchers suggested that these parameters are more useful in the determination of subjects with low bone health status.^[79–81,86]^

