### Statistical analysis

2.9

Data will be analyzed by using the IBM-SPSS software package (version 23.0). Descriptive data analysis will be reported by groups as means ± standard deviation for quantitative variables and as frequencies and percentages for qualitative variables. In the graphical representation, bar graphs by groups will be used for quantitative variables, and pie charts to represent categorical variables. The main change from baseline to 6 months will be calculated by using intention-to-treat analysis for each outcome measure.

Initially, for comparisons between groups at baseline, *t* tests or Mann–Whitney *U* tests will be used for continuous variables, depending on normality, which will be checked for each using the Kolmogorov–Smirnov test and normal probability box-plots, and the Chi-square test or Fisher test will be used for quantitative variables.

To analyze the efficacy of the multidomain intervention on the outcome variables, both in the primary and secondary outcomes, multivariate analysis of variance (MANOVA) will be applied with repeated measures (4 levels) to assess interactions between the factors and differences by categorical variables, with covariates, and pairwise comparisons post-hoc to determine whether there are significant differences between groups and within groups. The effect size for the MANOVA model will be calculated by the partial eta square (η^2^) that shows how much variance is explained by the independent variable.

We will carry out correlations with Pearson *r* coefficient to determine whether the values of 2 or more quantitative variables change in conjunction or are related in some of the moment of the study (time-factor in the statistical model).

For the analysis of the falls data, we will calculate the incidence rate during the study and the prevalence proportion by group and by sex at the end of the study (point prevalence). Subsequently, we will calculate the relative risk to estimate the magnitude of the association between the participation to the MPEP and falls, and indicate the likelihood of fall in the intervention group relative to the control group and also by sex.^[91]^

The statistical analysis will be conducted at a 95% confidence level. A *P* value < .05 will be considered to indicate statistical significance in all analyses.

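### Section 2.5 excludes patients who cannot do the evaluation tests without limiting this to baseline, so a randomised patient can be removed for failing on TUG or POMA-T, against the intention-to-treat analysis in section 2.9

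*Protocol article*

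**What the plan says.** Section 2.5 (Exclusion criteria) gives one list. Its second item is "Impossibility to carry out the evaluation tests", with no time point. The third is "Falls and other incidents or adverse events with severe consequences that cause disability and/or that do not allow the intervention to continue". The fourth excludes for attendance below 75% and carries the note "Criterion applied to each period between assessments". The fifth excludes for two or more consecutive weeks without sessions.

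Section 2.7.1 (Primary outcome variables) states: "Physical functions such as gait and balance will be assessed by the POMA-T and the TUG". Estimated BMD and T-score from calcaneal ultrasound are also primary. TUG is defined as the seconds taken to rise, walk 3 m, turn, return and sit, and the section adds that "values > 30 seconds indicate a high level of dependence". It gives no value for a patient who cannot complete the test. POMA-T is a sum of balance items (up to 16 points, including sitting balance) and gait items (up to 12).

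Section 2.9 (Statistical analysis) states: "The main change from baseline to 6 months will be calculated by using intention-to-treat analysis for each outcome measure". The efficacy model is a repeated-measures MANOVA over four time levels.

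The Introduction reports gait alterations in 50% of patients three years after diagnosis and says that "among these, 33% lose their capacity to walk".

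**The concern.** A patient who was testable at baseline and later cannot stand or walk has not merely missed a visit. Inability is failure on what TUG and POMA-T are meant to measure. If section 2.5 is applied to that patient, removal depends on the outcome itself, and the patients analysed in each arm are those who did well enough to be tested.

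The bias can run either way. If the programme preserves walking, more controls are removed and benefit is hidden. If more intervention patients become unable, for example after a fall, harm is hidden. If exclusion also ends assessment, falls and ultrasound results for those patients are lost although neither requires walking, and no later analysis plan can recover values that were never observed. A classical repeated-measures MANOVA uses only patients with all four values, so a patient unable at 6 months could lose the 1- and 3-month values as well.

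**Working it through.** **The texts side by side.** Items 3 to 5 of section 2.5 presuppose that the patient is already in the trial: an event that stops the intervention, attendance between assessments, and weeks without sessions. The list is therefore not an entry list only. Item 2 has no time point, so nothing in the text keeps it out of follow-up. Section 2.9 promises an intention-to-treat analysis of every outcome. Excluding randomised patients under section 2.5 and analysing all of them under section 2.9 cannot both be done.

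**The plan's own figure.** Section 2.8 uses a POMA-T difference of 1.5, SD 2, two-sided alpha 0.05, power 80% and dropout 33%.
- n per arm = 2 × (1.96 + 0.842)² × 2² / 1.5² = 27.9, rounded up to 28.
- 28 / 0.67 = 41.8, rounded up to 42 per arm, 84 in total.

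This matches the stated 84, so the point does not touch the sample-size arithmetic.

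**How often walking might be lost.** From the Introduction, 0.50 × 0.33 = 16.5% by three years after diagnosis. At a constant rate (assumption), six months gives 1 − (1 − 0.165)^(1/6) = 3.0%, or about 2 to 3 of 84 patients. The document gives no rate for this trial's own population.

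**Shift from cutting off the lower tail.** Assume POMA-T changes are normal with SD 2 and that the fraction p who become unable are those with the worst changes. Removing them raises the arm mean by SD × φ(z_p) / (1 − p).
- p = 3%: 2 × 0.0680 / 0.97 = 0.14 points.
- p = 1.5%: 2 × 0.0379 / 0.985 = 0.08 points.
- 3% against 0%: the difference shifts by 0.14 points, and 0.14 / 1.5 = 9% of the target.
- 3% against 1.5%: about 0.06 points, 4% of the target.
- Equal loss in both arms: no shift.

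**Shift if function collapses.** The tail formula takes the lost values from a normal curve with SD 2, so it may understate a collapse. As an upper illustration, assume a baseline POMA-T of 16 to 24 (not in the document) and a final total of 0. One such patient moves the mean of an arm of 42 by 16/42 = 0.38 to 24/42 = 0.57 points. At baseline 20 the figure is 20/42 = 0.48, so an imbalance of about three patients (1.5 / 0.48 = 3.1) equals the whole target effect.

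**What scoring a total of 0 would do to precision.** Assume a true effect of 1.5, 5% of each arm at a total of 0, 28 analysed per arm and a comparison of means. The SD rises from 2 to between 4.1 and 5.7 for baselines of 16 to 24, and power falls from 80% to between 25% and 15%. Scoring by item is less severe, because seated items still earn points.

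**The case against.** The strongest reply is that item 2 is an entry criterion. It follows directly after an ordinary screening item on pathologies that rule out exercise, and the authors wrote an explicit note on item 4 when they meant a criterion to run through follow-up. Section 2.9 also promises intention-to-treat. This stands as a possible reading. A reader might infer that the trial treats inability as missing data and that such a patient gets no score, but no section says so. The scoring of untestable patients may sit in an analysis plan that is not shown, and its absence from the article is no finding. What remains is that the wording permits post-randomisation exclusion and contradicts section 2.9 if used that way.

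A reader might also infer that loss of walking is the worst result on every primary endpoint. It is not. Calcaneal BMD and T-score do not need walking, POMA-T still gives a non-walker points for seated items, and among the secondary tests section 2.7.2 already counts a one-leg stand shorter than 5 seconds as a failure. Only TUG clearly lacks a value for inability.

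Larger effects are easy to produce. Loss of 10% against 0% gives 2 × 0.1755 / 0.90 = 0.39 points, 26% of the target. The document offers no source for such rates in six months.

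Finally, giving every untestable patient the worst score is one choice of estimand among several, and in a comparison of means it can cost much power, as shown above. That objection stands and shapes the fix.

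**Conclusion.** The point holds as an ambiguity with a real consequence. Section 2.5 does not confine inability to do the tests to baseline, the surrounding items operate after randomisation, and applying it there would remove patients for failing on TUG and POMA-T, in conflict with section 2.9. The direction of bias cannot be known in advance.

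The size is modest under the document's own figures: up to about 0.14 POMA-T points, 9% of the target, for 3% against 0%. This rests on a constant rate of loss, normal changes with SD 2, and the unable having the worst changes. It would be larger if loss of function is a collapse, since about three patients of imbalance could then equal the target effect under the assumed baseline of 20. The documents do not support the stronger conclusions that untestable patients are certain to be dropped, that all primary endpoints are affected, or that worst-score substitution is required. The change is worth making because it is cheap and settles either reading.

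**What to change.** - State in section 2.5 that inability to do the evaluation tests applies only at the baseline assessment, and reconcile the list with section 2.9 so that all randomised patients stay in the intention-to-treat set.
- Keep randomised patients who become unable in follow-up for all outcomes, including calcaneal ultrasound and falls. This concerns assessment only and says nothing about whether they continue the sessions.
- Score POMA-T by item, with items that cannot be performed at 0.
- Record 'unable' and the reason for each test at the visits already planned, and report the counts by arm and visit. Treat visits missed for other reasons as missing.
- Add a sensitivity analysis for TUG that ranks 'unable' below every completed time. A fixed ceiling near 30 seconds would not guarantee that order, because section 2.7.1 itself allows for completed times above 30 seconds.

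The cost is protocol wording, one extra form field and one extra analysis. The rank result for TUG is less direct to interpret than seconds, and the POMA-T SD may be larger than the 2 points assumed in section 2.8.

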#### Control group

2.6.2

Participants allocated to the control group will receive usual care and continue with their life normally, without participating in a standardized exercise program, and with the possibility to receive physical rehabilitation when needed. They will be instructed to maintain their current physical activity level, and will have to carry out the evaluations provided for in the study at 1, 3, and 6 months, with a periodic telephone contact. When the control patients are admitted to the Center-AD, they will have the opportunity to participate in the MPEP as well as the intervention group.

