### Sample size calculation

2.8

The sample size calculation has been made based on the potential modification of the score of the POMA-T. For this, we have considered the results obtained in the previous pilot study with 9 patients in a 1-month follow-up, and the preliminary trial with 72 participants with a ratio of 3:1 to the intervention group and the control one during 6 months. In the pilot study, the POMA-T was modified by 1.7 points. Then, in the preliminary trial, we accepted to calculate the sample size, as statistically significant, with a difference greater than or equal to 1.7 points with a dropTout rate of 15%.

In our current study, the sample size has been estimated to conduct a randomized controlled clinical trial with a 1:1 ratio between the 2 groups. In this new calculation, considering the data from the pilot study and some of the available data from the preliminary trial, we have reduced the minimal detectable change in the POMA-T to 1.5 points, with a standard deviation of 2 points and we have increased the drop-out estimated rate during the study to 33% by the difficulty to avoid intervention biases in the control group fundamentally. Therefore, with this, and accepting an alpha risk of 0.05 and a beta risk of 0.2 in a 2-sided test, 84 subjects are necessary, 42 in each group. The sample size calculation was made with the software “GRANMO sample size and power calculator” (7.12 version).

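### Attendance-based exclusions in section 2.5 operate only after randomisation and only in the intervention arm, which conflicts with the intention-to-treat analysis promised in section 2.9

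*Protocol article*

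**What the plan says.** Section 2.5 (Exclusion criteria) states that patients meeting any listed criterion are excluded. Four of the criteria concern us:

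- Attendance: "Attendance at the MPEP is less than 75% in the total of the sessions between assessments". The timing is explicit: "Criterion applied to each period between assessments".
- Missed sessions: "Not performing the MPEP sessions for 2 or more consecutive weeks".
- Severe events: "Falls and other incidents or adverse events with severe consequences that cause disability and/or that do not allow the intervention to continue".
- Other programmes: "Participate in another intervention program outside of this study, especially an exercise program (important intervention bias for the control group".

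Section 2.9 (Statistical analysis) says: "The main change from baseline to 6 months will be calculated by using intention-to-treat analysis for each outcome measure".

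Section 2.8 (Sample size calculation) explains the allowance for losses: "we have increased the drop-out estimated rate during the study to 33% by the difficulty to avoid intervention biases in the control group fundamentally". Section 3.1 (Strengths and limitations) adds that such biases can raise drop-out during follow-up.

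Falls during the study are a secondary outcome (section 2.7.2), with an incidence rate and a relative risk planned in section 2.9.

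**The concern.** An eligibility criterion should be decidable before allocation. The exercise programme starts after randomisation, so a rule on attendance at its sessions cannot be applied at entry, and no control patient can meet it. If the rule is followed as written, the intervention arm loses its poorest attenders while the control arm has no matching filter. People with dementia who attend poorly may well be those whose gait and balance are declining, so the patients left in the two arms would no longer be comparable by virtue of randomisation.

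The severe-event rule is tied to an outcome, since falls are counted and compared. The other-programme rule is aimed mainly at controls. The four rules therefore select differently in the two arms.

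An analysis cannot both drop randomised patients for non-adherence and analyse everyone as randomised. The primary comparison depends on which of the two is done.

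**Working it through.** **1. Which rules act after randomisation, and in which arm**

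| Rule in section 2.5 | Can it be an entry condition? | Arm affected |
|---|---|---|
| Attendance below 75% between assessments | No | Intervention only |
| 2 or more consecutive weeks without sessions | No | Intervention only |
| Severe fall or adverse event | Partly; the words on the intervention not being able to continue place it in follow-up as well | Continuation limb: intervention. Disability limb: either |
| Another programme | Partly; the drop-out reasoning in sections 2.8 and 3.1 places it in follow-up as well | Mainly control, by its own wording |

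Set against section 2.9, the first two rows are a direct contradiction. The last two are a contradiction so far as they act during follow-up.

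**2. The plan's own sample size**

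Inputs from section 2.8: difference 1.5 points, SD 2, two-sided alpha 0.05, power 0.80, ratio 1:1, drop-out 33%.

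- n per arm = 2 × [2 × (1.960 + 0.842) / 1.5]² = 27.9, rounded up to 28.
- 28 / (1 − 0.33) = 41.8, rounded up to 42 per arm, 84 in total.

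The stated 84 is reproduced. The arithmetic is right, but the 80% power belongs to about 28 analysed patients per arm who show the full 1.5-point effect. It makes no allowance for non-adherent or contaminated patients who stay in the analysis.

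**3. Illustration: bias if poor attenders are removed**

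Assumptions, none taken from the documents: no true effect; adherence and POMA-T change jointly normal with correlation ρ = 0.3 to 0.5; SD of change 2; the least adherent 20% of the intervention arm removed; 28 controls remain, and their loss has no selection effect.

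- Mean shift in adherence among those kept: normal density at the 20th percentile / 0.80 = 0.280 / 0.80 = 0.350 SD.
- Spurious benefit = 0.350 × ρ × 2, which is 0.21 points at ρ = 0.3 and 0.35 at ρ = 0.5.
- As a share of the 1.5-point target: 14% to 23%.
- Standard error = 2 × √(1/33.6 + 1/28) = 0.512, where 33.6 = 42 × 0.80.
- Two-sided type I error: 0.069 at ρ = 0.3 and 0.105 at ρ = 0.5, against a nominal 0.05.

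**4. Illustration: power if everyone is kept**

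Assumptions: all 42 per arm analysed with complete data, SD 2, and a share f of the 1.5-point effect lost. Power is from the two-sample t test.

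| f | Mean effect, 1.5 × (1 − f) | Power |
|---|---|---|
| 0 | 1.50 | 92% |
| 10% | 1.35 | 86% |
| 20% | 1.20 | 78% |
| 33% | 1.005 | 62% |

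The normal approximation gives about one percentage point more in each row (93%, 87%, 79%, 63%).

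**The case against.** The best defence is that the article states intention-to-treat for every outcome and nowhere says that data from excluded patients are discarded or their visits stopped. A reader might infer that intention-to-treat will certainly not be done. The text does not support that. Stopping the intervention while continuing assessment is a possible reading, though nothing in the article states it. What stands is that the sections conflict and the handling of excluded patients is not fixed. An analysis plan that is not shown could settle the handling, but it could not turn programme attendance into an entry condition.

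Four other stronger readings should also be resisted.

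- **All four rules are arm-specific and outcome-related.** Only the two attendance rules are strictly arm-specific, and only the severe-event rule is directly tied to an outcome.
- **A third of the intervention arm will be removed or gain nothing.** Section 2.8 attributes the 33% mainly to the control group, and the Discussion expects very high adherence at the Center. The 62% power is therefore the severe end of a range.
- **The falls comparison is distorted by a known amount.** Section 2.7.2 counts each subject's falls and the Discussion plans a falls registry, so the fall that triggers exclusion may well be counted. Any biased relative risk would have to assume that it is not, and that removal happens in one arm only.
- **The control group rules contradict each other.** Section 2.6.2 lets controls continue usual care "with the possibility to receive physical rehabilitation when needed". Section 2.5 concerns programmes outside the study. The two are compatible as written.

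**Conclusion.** The point holds. The two attendance rules cannot be eligibility criteria, and applying them as written would break the randomised comparison that section 2.9 promises. The severe-event and other-programme rules add to the conflict so far as they act during follow-up. Sections 2.5, 2.8 and 2.9 must be reconciled. This is a rule stated wrongly in the current text, so it is more than a missing detail.

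Neither the direction nor the size of the net bias can be derived from the documents, because losses in the control arm may select as well. The spurious benefit of 0.21 to 0.35 points, with type I error of about 7% to 10.5%, rests on an assumed 20% removal, an assumed correlation and neutral control losses. Under full retention, power stays close to or above 80% for dilution up to about 20% and falls to about 62% at 33%.

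**What to change.** The change concerns follow-up and analysis only, not when treatment should stop.

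1. Restrict section 2.5 to conditions present before randomisation.
2. List low attendance, 2 or more missed weeks, severe falls or adverse events, and joining another programme as post-randomisation events. State that patients who have them are still assessed at 1, 3 and 6 months where able, and are analysed in the arm to which they were allocated.
3. Use the 75% attendance rule only to define a secondary per-protocol analysis.
4. State that all falls are counted, including any that would have triggered exclusion.
5. Add to section 2.8 that the 80% power refers to about 28 analysed patients per arm with the full 1.5-point effect, and give the power expected with everyone retained over a plausible range of dilution.

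The cost is mainly wording. The visits are already scheduled, so the added work is following patients who would otherwise have been dropped. The expected effect, and with it the stated power, may become less favourable.
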